## Methods

### Data Collection

#### Setting and Participants

This is a quasi-experimental study. This protocol is version 1.0, finalized on July 8, 2025. We will select children with malignant tumors and their family caregivers who were hospitalized at West China Second Hospital, Sichuan University, between July 2025 and December 2026. Family caregivers of the children will be enrolled. The researchers will provide a detailed description of the study’s purpose and content to the participants, who must sign an informed consent form.

The QR code for the web-based questionnaire will be distributed after caregivers provide informed consent. The family caregivers recruited for the study will be divided into control and intervention groups. Children will be grouped according to their diagnosis and treatment timeline as follows: children admitted from July to December 2025 will form the control group, and those admitted from July to December 2026 will form the intervention group. The caregivers of the children will be enrolled along with the children. In the intervention group, the intervention program will be implemented after inclusion. For the control group, where routine health promotion is implemented, an intervention program based on FCEM will be offered upon the second admission to the hospital (Figure 1).

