**Figure 1 figure1:**
[figure not shown]
Participant timeline.

After the family caregivers complete the baseline survey, the researchers will distribute paperwork or provide verbal health promotion with relevant health promotion components and assess the caregivers’ knowledge weekly.

The questionnaire will be re-administered 3 days before the child is discharged. One researcher will enter the data, which will be double-checked for errors by another researcher. After all data are entered, the analysis will be performed by a designated specialist who remains unaware of the groupings. Finally, 2 additional researchers will independently review the analyses to ensure accuracy. Family caregivers will be aware of their grouping. If family caregivers prefer to adjust their groupings, appropriate adjustments will be made based on their identified needs.

The inclusion criteria are as follows: (1) children aged 0-18 years, (2) children clinically diagnosed with malignant neoplasms, and (3) first-time visitors to our hospital.

The exclusion criteria are as follows: (1) children diagnosed and treated with radiotherapy or chemotherapy in other hospitals and (2) children undergoing their first treatment in our hospital for recurrence of the disease.

Primary caregiver inclusion criteria are as follows: (1) the caregiver is enrolled along with the child, (2) the caregiver is aged 18 years or older, (3) the caregiver is a member of the child’s immediate family, (4) the caregiver has cared for the child for the longest period among multiple caregivers, (5) the caregiver has basic communication and reading skills and is proficient in Chinese, and (6) the caregiver has no previous history of psychiatric illness or consciousness-related disorders.

The sample size was calculated to be 128 using G*POWER 3 software [10] with the parameters α=.05, 1 – β=0.8, and effect size=0.5. Considering a 10% lost-to-follow-up rate, the total sample size required was estimated to be 142, with 71 caregivers in the intervention group and 71 in the control group.

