#### Sociodemographic Variables

Sociodemographic variables in patients (including age, sex, ethnicity, medical payment method, clinical diagnosis, and duration of disease) and their caregivers (including age, relationship with the patient, ethnicity, place of residence, number of children, marital status, level of education, occupation, monthly family income, caregiving experience, number of other persons in need of care, hours of care per day, health status, disease awareness, and access to information) will be recorded. Disease-related variables will be obtained from the consent forms signed by the patients and their guardians.

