### Data Analysis

Data will be analyzed using SPSS version 26.0 (IBM Corporation). For general information, measurement data conforming to a normal distribution will be described by means and SDs, and count data will be described by frequencies and constitutive ratios. Missing data will be removed and will not be included in the analysis. Participants who request to switch groups based on their preferences will be excluded from the primary analysis; however, we will summarize the baseline characteristics of these participants and compare them to those who remain in their originally assigned groups. This comparison will include demographics to assess the potential impact of nonrandom attrition on study validity.

Independent-sample *t* tests will be used to compare caregiving preparedness, caregiving capacity, self-efficacy, and depression, anxiety, and stress scores between the 2 groups before the intervention. After the intervention, both within-group and between-group differences in these variables will be analyzed using independent-sample *t* tests, paired *t* tests, Mann-Whitney tests, and paired rank-sum tests.

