### Limitations

This study has several limitations. First, the intervention will be implemented for family caregivers of children with malignant neoplasms rather than targeting a specific cancer type, and caregivers of children with different cancer types may face distinct challenges. Second, the intervention period is relatively short, limiting the ability to observe the long-term effects of the FCEM intervention program on family caregivers. Finally, as this is a single-center study conducted at 1 hospital, the findings will reflect only the situation at this center. Considering geographic variations in the level of medical care, the findings may not be generalizable to primary care settings or populations with different cultural or socioeconomic backgrounds. In the future, the study could be expanded to include multiple centers. To further enhance the evaluation and adaptation of empowerment strategies, it is also recommended that future studies involve caregivers of children with various types of cancer.

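### Two non-randomised cohorts admitted a year apart are compared only with unadjusted tests, so measured case-mix differences enter the estimated intervention effect

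*Protocol article*

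**What the plan says.** Under Setting and Participants the article declares the design ("This is a quasi-experimental study") and allocates by admission date: "children admitted from July to December 2025 will form the control group, and those admitted from July to December 2026 will form the intervention group". These periods do not overlap. Children aged 0-18 with any malignant neoplasm are eligible.

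Data Analysis has independent-sample t tests compare the outcome scores of the two groups before the intervention. For the period after it, "both within-group and between-group differences in these variables will be analyzed using independent-sample" and paired t tests, together with their rank-based counterparts (Mann-Whitney for two groups, a paired rank-sum test within a group). The Methods paragraph of the abstract gives the same list. Neither place names a covariate, regression model, matching, weighting or stratification.

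Sociodemographic Variables lists what could be adjusted for. For the child this includes age, diagnosis and disease duration. For the caregiver it includes "level of education, occupation, monthly family income, caregiving experience, number of other persons in need of care, hours of care per day".

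Limitations names three items: mixed cancer types, a short intervention period, and the single centre ("as this is a single-center study conducted at 1 hospital, the findings will reflect only the situation at this center"). It mentions neither the non-random allocation nor the non-concurrent control.

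**The concern.** Group and admission year coincide, so any difference between the 2025 and 2026 cohorts in diagnosis mix, caregiver education or starting preparedness is part of the contrast being tested. The Limitations section itself says that challenges may differ by cancer type, which makes diagnosis mix a plausible confounder on the article's own account. A two-sample test of post-intervention scores cannot separate such differences from the programme. The paired tests work within one group, so they do not address confounding between groups.

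At stake is the main between-group conclusion: the abstract expects significantly greater improvement than in controls. The data needed to remove the measured part of the imbalance are already being collected.

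**Working it through.** **Inputs from the article** (Setting and Participants, text after Figure 1): α = 0.05, power 0.80, effect size 0.5, 10% loss, 71 per group.

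**Inputs assumed** (the article gives none): between-year shift s in the baseline score, 0.2 or 0.3 SD; baseline-to-outcome correlation r, 0.3 to 0.7; within-group SD 1.

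**1. The plan's own figure.** "The sample size was calculated to be 128 using G*POWER 3 software". A two-sided two-sample t test (noncentral t) with d = 0.5 needs 64 per group, 128 in total, with power 0.8015. A one-sided test would need 102 in total and a paired test 34 pairs, so the sizing assumes an unadjusted two-sided comparison. 128 / 0.9 = 142.2, which agrees with the stated 142 to rounding.

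**2. Unadjusted test, no true effect.** A baseline shift s moves the mean outcome by s × r. The rejection rate is the power of the t test at d = s × r with 64 per group.

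| s | r | s × r | Rejection rate |
|---|---|---|---|
| 0.2 | 0.3 | 0.06 | 6.3% |
| 0.2 | 0.5 | 0.10 | 8.7% |
| 0.2 | 0.7 | 0.14 | 12.3% |
| 0.3 | 0.3 | 0.09 | 8.0% |
| 0.3 | 0.5 | 0.15 | 13.4% |
| 0.3 | 0.7 | 0.21 | 21.8% |

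In simulation (4,000 runs each), ANCOVA on the baseline score rejected at 4.3% to 5.2% across these six cases.

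**3. Power of ANCOVA at d = 0.5.** The residual SD is √(1 − r²), so the standardised effect becomes 0.5 / √(1 − r²).
- r = 0.3: 0.524, power 0.84
- r = 0.5: 0.577, power 0.90
- r = 0.7: 0.700, power 0.98

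The unadjusted test has 0.80. The planned 142 caregivers are enough for an adjusted analysis.

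**4. What a baseline t test can show.** With 64 per group it detects a true 0.3 SD imbalance with probability 0.39. A non-significant result would not demonstrate balance.

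**5. What adjustment cannot repair.** Take an outcome shift of 0.3 SD due to calendar time and unrelated to baseline. The unadjusted test rejects at 39%. With r = 0.5, ANCOVA faces 0.3 / 0.866 = 0.346 and rejects at 49%: the bias is the same and the standard error smaller.

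**6. Timing of the baseline score.** The abstract places the first questionnaire 3 days after admission. Intervention Group puts stage 1 within 3 days of admission. The text after Figure 1 puts health promotion after the baseline survey. These are not reconciled. If stage 1 had already raised the baseline by 0.2 SD (assumed) and the true effect is d = 0.5 with r = 0.5, ANCOVA estimates 0.5 − 0.5 × 0.2 = 0.40. The standardised effect is 0.40 / 0.866 = 0.462, and power is 0.74, below the unadjusted 0.80.

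**The case against.** - **Scope.** A condensed article may leave covariate lists and sensitivity analyses to a fuller plan. That covers detail but not this choice: the article twice states which tests will compare the groups, and its sample size matches them.
- **Design safeguards.** Both waves use the same July-December window, hospital and eligibility criteria, and the study calls itself quasi-experimental. This limits seasonal differences. It does not address year-to-year differences in case mix or care.
- **Magnitude.** A reader might infer false-positive rates of 20% or 39%, from an outcome shift of 0.2 or 0.3 SD. The article gives no basis for shifts of that size, and such rates do not measure what baseline adjustment repairs. The repairable part is that in step 2 of the working.
- **Use of baseline data.** A reader might say the baseline data go unused. They do not: scores are compared between groups and enter the paired tests, and characteristics are described and used to compare group-switchers with the rest. What is missing is their use in the between-group estimate. Nor does the article say that a non-significant baseline test will be taken as balance.
- **Two tests for one contrast.** Naming both t and rank tests might suggest that the smaller p value will be reported. Nothing in the article says so. A choice by distribution is the ordinary reading, although the rule is not written down.
- **Cost of covariates.** Multi-category covariates use degrees of freedom, which is a reason to keep the list short. Even ten covariate parameters would leave 128 − 2 − 10 = 116.
- **Baseline timing.** This objection stands: the timing has to be settled before the score is used as a covariate.

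**Conclusion.** The concern holds for the between-group comparison. As stated, the analysis lets measured differences between the 2025 and 2026 cohorts pass into the estimated effect, and the Limitations do not disclose the non-concurrent control. Under the assumed shifts and correlations the excess false-positive risk is modest to substantial, and ANCOVA returns it to the nominal level when the imbalance lies in the adjusted baseline score. The power gain depends on a baseline taken before any intervention content.

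It would go too far to infer that adjustment makes the comparison equivalent to a randomised one. Calendar-time changes unrelated to measured variables are inseparable from group and remain. The sample size is not in error.

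**What to change.** 1. Reconcile the abstract, the text after Figure 1 and the stage 1 description on when the first questionnaire is completed. The score can serve as a baseline covariate only if it is taken before stage 1.
2. Make the primary between-group analysis a prespecified linear model (ANCOVA) of the post-intervention score on group. Adjust for that outcome's baseline score and a short fixed set of collected covariates, for example diagnosis group, child age, caregiver education and caregiving experience. Report the adjusted difference with its 95% CI.
3. Keep baseline comparisons descriptive, and do not treat significance tests as evidence of balance.
4. State the non-concurrent, non-randomised control as a limitation, and word conclusions as association.

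No new data, visits or participants are needed. The cost is revised analysis wording, some degrees of freedom and a more modest claim. The covariate list should be fixed before outcomes are examined, since one chosen afterwards would carry little weight.

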### Ethical Considerations

This study was approved by the Ethical Review Committee of West China Second Hospital of Sichuan University (approval number YXKY2024432). The trial was registered on February 5, 2025, with ClinicalTrials.gov (NCT06810388). Before data collection, the study leader will obtain written informed consent from all participants. Participants will also be informed in advance that they will be contacted for a follow-up assessment approximately 1 month after discharge.

During the study, personal information, such as names, gender, and other identifiers of participants and their children, will be replaced with codes or numbers to maintain confidentiality. Access to this information will be limited to authorized researchers, ensuring the privacy of participants and their children is fully protected. While the study results may be published in academic journals, no personal details of the participants will be revealed.

All participants will be informed of their right to withdraw from the study at any time and that completing the questionnaire will not affect their children’s medical or nursing care. All family caregivers in the control group will be asked if they would like to receive the family empowerment intervention program upon their second admission, which the researchers will provide.

## Results

### Recruitment Progress

The study was approved by the Ethical Review Committee of West China Second Hospital of Sichuan University on January 9, 2025 (approval number YXKY2024432). We plan to recruit participants for the control group from July to December 2025. We will recruit caregivers for the intervention group from July to December 2026. Data collection will occur throughout the recruitment period. Results are expected to be published in late 2027.

### Caregiving Preparedness and Capacity

We expect caregivers in the intervention group to have higher preparedness and caregiving capacity than those in the control group. In addition, significant improvement is expected within the intervention group after the intervention.

### Self-Efficacy Outcomes

Regarding the self-efficacy outcomes, caregivers receiving the intervention are likely to show increased self-efficacy after discharge. No major change is expected in the control group.

### Psychological Outcomes

Caregivers in the intervention group are expected to report significantly lower depression, anxiety, and stress scores after the intervention.

## Discussion

### Principal Findings

The intervention based on the FCEM model is expected to improve caregiving preparedness, caregiving capacity, and self-efficacy in family caregivers of children with malignant neoplasms. It may also reduce their psychological distress, including symptoms of depression, anxiety, and stress. These anticipated findings will contribute to enhancing the design and implementation of family-centered interventions in pediatric oncology care.

The results of this study will be shared with the Department of Pediatric Hematology and used to refine and improve existing health promotion strategies.

### Limitations

This study has several limitations. First, the intervention will be implemented for family caregivers of children with malignant neoplasms rather than targeting a specific cancer type, and caregivers of children with different cancer types may face distinct challenges. Second, the intervention period is relatively short, limiting the ability to observe the long-term effects of the FCEM intervention program on family caregivers. Finally, as this is a single-center study conducted at 1 hospital, the findings will reflect only the situation at this center. Considering geographic variations in the level of medical care, the findings may not be generalizable to primary care settings or populations with different cultural or socioeconomic backgrounds. In the future, the study could be expanded to include multiple centers. To further enhance the evaluation and adaptation of empowerment strategies, it is also recommended that future studies involve caregivers of children with various types of cancer.

### Strengths

The methodological strength of this study lies in the establishment of an intervention program tailored to the needs of family caregivers of children with malignant neoplasms. The program includes caregiving knowledge, skills, and psychological coping strategies to enhance the educational content of the family empowerment program. Designed for caregivers of children with various types of malignant neoplasms rather than a single type, the intervention program aims to contribute to a more comprehensive health education system and facilitate future replication.

### Future Directions

To further expand the impact of such interventions, future studies may consider integrating emerging technologies into caregiver support strategies. As digital health tools continue to evolve, there is growing interest in leveraging emerging technologies to enhance caregiver support [20,21]. With the rapid development of large language models, future studies may consider exploring the integration of large language model–based tools to further support family caregivers.

## Appendix

Multimedia Appendix 1 Theoretical framework mapping the family-centered empowerment model to the phases of the intervention.

Multimedia Appendix 2 Family caregiver mastery evaluation form (weekly).

Multimedia Appendix 3 Routine health education content for the control group.

Multimedia Appendix 4 Sample informed consent form.

## Abbreviations

FCEM: family-centered empowerment model
PICC: peripherally inserted central catheter
